### Study setting

The UniTest Study will conduct in 4 provinces based on geographical location and distribution of colleges and universities (Table 1).

**Table 1 Tab1:** Study setting of the UniTest Study

Area	Location	CDC/CBOs	Sample size
Southern	Guangdong province	Lingnan parners Pengyou care Nanshan Center for Chronic Disease Control	112
Western	Chongqing municipality	Chongqing CDC	112
Northern	Tianjin municipality	Tianjin CDC Shenlan	112
Eastern	Shandong province	Qingai	112

*CDC* Center for disease control

*CBOs* Community-based organizations

The UniTest Study began in November 2018 and is scheduled to complete by December 2020. The study has four study phases, including enrollment, baseline survey, follow-up survey and intervention, and 12 months end-point survey (Fig. 1).

**Fig. 1 Fig1:**
[figure not shown]
The flow chart of the UniTest study. Enrollment procedure: This section includes recruitment, screening, informed consent, and registration. Baseline survey procedure: This section includes a baseline questionnaire and sampling testing. Follow-up survey and intervention procedure: This section is divided into two parallel parts, including questionnaire follow-up and the stepped wedge trial designed HIV self-testing intervention. End-point survey procedure: This section includes 12 months follow-up questionnaire and sampling testing

### Enrollment procedure

Participants recruitment will be promoted both online and offline. For online: study advertising campaigns will be placed on the social network such as WeChat [31, 32] (WeChat is a Chinese multi-purpose messaging, social media and mobile payment app developed by Tencent Inc., Shenzhen, China.) and gay community web pages. For offline: the study advertisement will be distributed with the collaboration of community-based organizations (CBOs), health clinics, and student associations. A WeChat account will be established solely for online consultation and follow-up. After reading study advertisement online or offline, potential participants can learn more about the study through the contact information on the advertisement and make an appointment to join the study at a preferred CBO.

Participants will complete the screening procedure and receive a rapid test at a given CBO. An online registration page will guide each participant to complete the sign-up process, including the UniTest Study introduction, eligibility assessment, informed consent, study identification (ID) number assignment, and mobile phone number verification.

### Questionnaire survey

We will use a self-administrated online questionnaire to record the information of participants. After scanning the Quick Response (QR) code by mobile phone, participants can verify their identities and fill in the questionnaire. The questionnaire contains different structured modules with the behavioral intervention theory design (Table 2). Participants will complete a self-administrated online questionnaire onsite at baseline and 12-month follow-up and complete an online questionnaire at 4- and 8-month.

**Table 2 Tab2:** Summary of variables collected at baseline and follow-up visits

Variable modules	Time point(s)
Personal verification information	Baseline
Socio-demographic information	Baseline
Sexual behavior information	Baseline/Follow-up
Social media use behaviors	Baseline/Follow-up
Self-cognition scale	Baseline
HIV infection susceptibility/severity perception scale	Baseline/Follow-up
HIV testing obstacle perception scale	Baseline/Follow-up
HIV testing benefit perception scale	Baseline/Follow-up
HIV testing self-efficacy scale	Baseline/Follow-up
HIV testing behaviors	Baseline/Follow-up
Others: STIs, alcohol use, drug use	Baseline/Follow-up

### Sampling and testing

We will collect blood specimen and rectal swab specimen on-site at baseline and 12-month follow-up visits. Trained doctors will collect 10 ml blood specimen and conduct HIV rapid testing. Participants will self-collect a rectal swab guided by a self-collection instruction (see Additional file 2) [33].

Specimens will be labelled with unique survey ID numbers that match the participant’s laboratory requisition form, questionnaire, and results form. No personally identifying information will be included on any specimen, or laboratory form.

Blood specimens will be tested for hepatitis A (HAV), hepatitis B (HBV), and hepatitis C (HCV) in the certified laboratory (Hybribio Medical Laboratory, Guangzhou, China). The HAV, HBV, and HCV status will be determined by Enzyme-linked immunosorbent assay (ELISA) (Autobio Biological engineering co., Ltd., Zhengzhou, China).

Rectal swab specimens will be collected to test for thirty-seven subtypes of human papilloma virus (HPV), including HPV6, 11, 16, 18, 26, 31, 33, 34, 35, 39, 40, 42, 43, 44, 45, 51, 52, 53, 54, 55, 56, 57, 58, 59, 61, 66, 67, 68, 69, 70, 71, 72, 73, 82, 83, 84, CP8304. HPV status will be determined by Polymerase chain reaction (PCR) (Hybribio Biochemical co., Ltd., Chaozhou, China).

### HIV testing

The HIV testing will be conducted with rapid HIV testing (Alere® Determine HIV-1/2, Alere Medical Co., Ltd., Matsudo, Japan) at baseline and 12-month follow-up. Participants tested HIV negative result will be included in the cohort. Participants tested positive for HIV will be referred to local centers for disease control and prevention for confirmation testing and subsequent services as per guidelines (*Regulations on the Prevention and Control of AIDS)* [34].

### Intervention process

HIVST intervention process will last for six months, including HIV testing reminders, HIVST kit distribution, and HIVST result feedback (Fig. 2).

**Fig. 2 Fig2:**
[figure not shown]
The flow chart of the HIV self-testing intervention

#### Intervention group

Once allocated to the intervention group, participants will be provided HIV self-testing comprehensive Intervention, including HIVST kits with testing and feedback reminders. We encourage our participants to perform HIV tests for themselves and their sexual partners with HIVST kits. At each intervention, participants will be provided two HIVST kits along with instructions. Each participant will receive up to two deliveries of a total of four HIVST kits during 6 months intervention period.

#### HIV self-testing kit

A finger-prick-based HIV self-testing package contains an HIV testing kit (Alere® Determine HIV-1/2, Alere Medical Co., Ltd., Matsudo, Japan), band-aid, alcohol pad, disposable peripheral blood needle, and operation instruction card. The HIVST kit was a third-generation rapid reagent approved by the US Food and Drug Administration (FDA) and China State Food and Drug Administration (CSFDA), it can detect HIV 1/2 antibodies in blood specimens at six weeks post-infection. The specificity and sensitivity of the Alere® Determine HIV 1/2 are 99.75 and 100%, respectively. The testing result can be read in 15–60 min [35].

#### HIVST kit distribution

A reminder to test for HIV will be sent to a participant via WeChat on the first day of enrollment. This opt-out reminder will be sent at 15-day intervals until participants apply for the HIVST kit. After receiving the message, the participant can click the link to fill out information for applying for HIVST kit. HIVST kits will be delivered anonymously and confidentially via post express.

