### Control group

Participants who are waiting for randomized allocation of intervention, are treated as control group that will not receive HIVST intervention. These men will need to complete a questionnaire at 4- and 8-months.

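### The trigger for the HIV-test reminder and kit link is tied to enrollment, not to the allocated step; followed literally, it puts an intervention component into control time

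*Protocol article*

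**What the plan says.** All references are to the protocol article.

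- **HIVST kit distribution** sets the trigger: "A reminder to test for HIV will be sent to a participant via WeChat on the first day of enrollment". It then sets the repetition and the stop: "This opt-out reminder will be sent at 15-day intervals until participants apply for the HIVST kit". The message opens the route to a kit: "After receiving the message, the participant can click the link to fill out information for applying for HIVST kit".
- **Intervention process** makes the reminder part of the intervention: "HIVST intervention process will last for six months, including HIV testing reminders, HIVST kit distribution, and HIVST result feedback".
- **Intervention group** gives a different start: "Once allocated to the intervention group, participants will be provided HIV self-testing comprehensive Intervention, including HIVST kits with testing and feedback reminders".
- **Control group** says that men waiting for their allocation "are treated as control group that will not receive HIVST intervention".
- **Fig. 1 legend** defines the word on which the trigger rests: "Enrollment procedure: This section includes recruitment, screening, informed consent, and registration". Study setting lists enrollment as a phase of its own, ahead of the baseline survey and of the phase that holds the intervention. Enrollment procedure uses the word in the same sense. The Discussion has participants connect to the WeChat study account during enrollment.
- **Outcome measures and Table 3** make the primary outcome the change in testing frequency from before to after the intervention. Control time is the wait for the intervention. Reminders and kit applications are counted over the whole study period.

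**The concern.** In a stepped-wedge trial the effect is identified by the difference between time before and time after the allocated step. A message that tells a man to test acts directly on testing frequency, which is the primary outcome. If the message goes out from study entry, control time already holds one part of the package under test, and the contrast no longer measures the whole package.

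The link raises a separate problem. No section shown says that it is inactive during the wait. A man who uses it early would reach the kits before his randomised step, and the allocated order would no longer decide who is exposed when.

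An analysis plan could not settle this afterwards. It is an operational rule, and control time in which reminders have been sent cannot be made unexposed by analysis.

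**Working it through.** **1. The sections side by side.**

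| Section | When reminders start | Waiting men reminded? |
|---|---|---|
| Intervention process | Not dated; reminders are a component | No, if waiting men get no intervention |
| Intervention group | At allocation to the intervention | No |
| Control group | Not dated; no HIVST intervention while waiting | No |
| HIVST kit distribution, enrollment = study entry | At study entry | Yes |
| HIVST kit distribution, enrollment = entry to the step | At the allocated step | No |

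The first three rows agree. The conflict appears only under the fourth, and the fourth is how the article uses the word everywhere else.

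**2. Reminders before crossing over, under the literal reading.** Inputs: reminders on days 0, 15, 30 and so on (HIVST kit distribution); steps 30 days apart (Study design); six intervention periods (Sample size). Two assumptions are needed. The day of the first step is not given, so both obvious choices are shown. Steps are counted from the participant's own enrollment day. Counting reminder days strictly before the crossing day:

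- Steps at days 30, 60, …, 180: 2, 4, 6, 8, 10, 12; mean 42/6 = 7.
- Steps at days 0, 30, …, 150: 0, 2, 4, 6, 8, 10; mean 30/6 = 5.

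These are maxima, because reminders stop once a man applies for a kit.

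**3. What dilution would cost.** Inputs from Sample size: control 0.40, intervention 0.60, two-sided alpha 0.05, power 90%. The planned contrast is 0.60 − 0.40 = 0.20. The 90% is taken as given; the stated 408 is not used. The formulas tried here did not reproduce 408, but its derivation is referred to an additional file that is not shown, and this point does not depend on it.

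Let reminders alone remove a share *s* of the contrast, so that control testing becomes 0.40 + 0.20*s* with 0.60 held fixed. Treating the standard error as unchanged:

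- power = Φ[(1.960 + 1.2816)(1 − *s*) − 1.960]
- factor on N needed to restore 90% = 1/(1 − *s*)²

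| *s* | Control rate | Contrast | Argument of Φ | Power | N factor |
|---|---|---|---|---|---|
| 0 | 0.40 | 0.20 | 1.282 | 90% | 1.00 |
| 0.1 | 0.42 | 0.18 | 0.957 | 83% | 1.23 |
| 0.2 | 0.44 | 0.16 | 0.633 | 74% | 1.56 |
| 0.3 | 0.46 | 0.14 | 0.309 | 62% | 2.04 |
| 0.4 | 0.48 | 0.12 | −0.015 | 49% | 2.78 |
| 0.5 | 0.50 | 0.10 | −0.339 | 37% | 4.00 |

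**4. Cross-check with the stepped-wedge variance.** The Hussey-Hughes formula with six clusters, seven periods and a coefficient of variation of 0.4 on the control rate needs 19 men per cluster-period at 0.40. It needs 24 at 0.42, 40 at 0.46 and 78 at 0.50. The ratios 24/19 = 1.26, 40/19 = 2.11 and 78/19 = 4.11 agree with the factors above.

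The values of *s* are assumed. The documents say nothing about how far a reminder alone raises testing.

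**The case against.** The strongest reply is that one loosely used word is being made to carry too much. The kit-distribution text is a subsection of the intervention description and follows the subsection on the intervention group, while the control group has a separate section after it. In that position, the participant who receives the reminder is most naturally someone already in the intervention, and enrollment would mean entry to it. Intervention group states the start rule outright. Read literally, the trigger would let every man apply for kits from the outset, leaving little of the waiting list or the control time. A wording slip is more plausible than a design that defeats itself. The flow charts, which might show the real trigger, are not available here.

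Most of this stands. A reader might infer that waiting controls do receive reminders and that the estimate is diluted. The documents do not support that: two sections say the opposite, and the third can be read to agree with them. Nor do all the sections contradict one another; only the literal reading of the trigger is out of line. The count over the study period in Table 3 fits either reading.

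The direction of bias also needs care. Reminders in control time would tend to pull the contrast toward no effect. Early kit requests need not. Table 3 divides time by actual receipt of the intervention, so an early applicant could be counted as intervention time. That introduces self-selection, with bias of uncertain direction.

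What does not stand is the view that nothing needs correcting. The article's other uses of enrollment all mean study entry, the messaging channel is open from then, and no section shown disables the link during the wait. Staff who set up the messages from this text could reasonably start them at study entry.

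**Conclusion.** The point holds as an internal contradiction about when the reminder and the kit link start, with a conditional consequence. If reminders begin at the allocated step, there is no dilution and the planned contrast of 0.20 is untouched. If the enrollment trigger is followed literally, waiting men receive up to 2 to 12 reminders each (0 to 10 with the first step at day 0), and the allocated order can be broken by early kit requests.

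The loss of power runs from 90% to about 83%, 62% and 37% for control rates of 42%, 46% and 50%. Those rates are assumptions, as are a fixed intervention rate of 60% and a design that has exactly its stated power. The contradiction itself rests on none of these figures. It deserves correction because the reminder acts on the primary outcome and the trial is already enrolling.

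**What to change.** Reconcile HIVST kit distribution with Intervention process, Intervention group, Control group and the Table 3 indicators:

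1. Replace the enrollment trigger with the first day of the participant's allocated intervention step, and state that the application link is inactive before that day.
2. Log every reminder sent and every kit application made before the allocated step. In Table 3, count reminders and applications separately for control time and intervention time.
3. Analyse by allocated step, not by actual receipt, so that any early application does not move a man's time between conditions.
4. If reminders do in fact go to everyone from study entry, say so, and state that the estimated effect is that of kit availability on top of reminders, not of the whole package.

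The cost is about one sentence in the protocol, a check of how the WeChat messages are triggered, and a log. If messages have already gone out during control time, a change of trigger protects only later time; the log then shows how much control time was affected.

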#### HIVST result feedback

Participants will be guided by either the printed instruction included in the kit package or an online demonstration video by scanning the QR code, to complete self-testing procedures.

After finishing self-testing, participants can upload the testing results via the online feedback system. The system will record the test results filled in by the participants themselves; then research staff will conduct a doubled check for the results.

A feedback reminder will send a message to the participant after confirming receiving HIVST kit. If the participant has not uploaded his testing result, the feedback reminder will repeatedly send text in every 15 days.

### Control group

Participants who are waiting for randomized allocation of intervention, are treated as control group that will not receive HIVST intervention. These men will need to complete a questionnaire at 4- and 8-months.

### Study endpoint

HIV positive: Participants who have positive results with HIVST will be provided with further consultation for the testing results and recommendations to local CDC for confirmatory laboratory testing. If the participants are laboratory confirmed HIV positive, the study process (follow-up and intervention) will be discontinued.Loss to follow-up.Close-out of study: Participants finish 12-month follow-up and testing.

### Outcome measures

The primary outcome is the change in frequency of HIV testing comparing before and after intervention. Secondary outcomes include the change in sexual behaviors comparing before and after intervention, and HIV incidence comparing before and after intervention (Table 3).

**Table 3 Tab3:** Key indicators of the UniTest Study

Indicators		Definition
HIV testing Behavior	HIV testing in the control group	The frequency of HIV testing before receiving the intervention
	HIV testing in the intervention group	The frequency of HIV testing after receiving the intervention
	HIV testing reminders	The frequency of sending HIV testing reminders during the study period
	HIV self-testing kit application	The frequency of self-testing kits applications during the study period
	HIV self-testing result feedback	The frequency of self-test results feedback during the study period
Time indicator	Control time	The time interval of the participants to wait for receiving the intervention
	Intervention time	The time interval of the participants from receiving the intervention to the endpoint
HIV testing result	HIV infections	HIV infections detected during the study period
	HIV infections in the control group	HIV-positive individuals tested before intervention
	HIV infections in the intervention group	HIV-positive individuals tested after intervention

### Data management and statistical analysis

All data will be recorded directly in the online database (www.wjx.cn, Ranxing information technology co., Ltd., Changsha, China). The database system automatically saves the data and ensures the security, integrity, and consistency of the data. The network server is hosted in Alibaba Cloud (Alibaba Group, Hangzhou, China) and installed with enterprise firewall protection, while the daily backup mechanism ensures data security. The data have multiple levels of permission settings and password protection to ensure data security.

In the statistical analysis, the general statistical analysis will be carried out by using standard statistical software and professional statistical software. If more advanced statistical methods are needed to complete the data processing and utilization, the training of data analysis and utilization can be added.

### Descriptive statistical analysis

The analysis will be carried out for all variables and outcomes involved in the study according to the types of variables, including count, frequency, ratio, mean, standard deviation, and so on.

### Latent variable analysis and structural equation model

We will conduct a latent variable analysis to explore the indicators and connected potential variables. After the latent variable analysis, the path analysis diagram will show the relationship between potential variables and explicit variables in the structural equation model. We will use structural equation model (SEM) to evaluate the effect of HIVST intervention, estimate the association among behavioral intervention theory modules (such as social demographic characteristics, social cognition, social norms, susceptibility to perceived HIVST benefits, self-efficacy, etc.), sexual behavior, HIV testing behavior, HIV infection, and HIVST. Meanwhile, multiple model fitting and comparison will be conducted to select the best model that can explain the effect and influencing factors of HIVST intervention among MSM attending university in China.

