### Missing data

We will record the reasons for missing data. Multiple imputation (MI) methods will be conducted to increase the robustness of study results.

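### The stated effect analysis, a structural equation model chosen by comparing fits on the trial data, does not secure the randomised total effect on HIV testing frequency

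*Protocol article*

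**What the plan says.** Outcome measures sets the target: "The primary outcome is the change in frequency of HIV testing comparing before and after intervention". Study design states that the order of starting the intervention is what is randomised, with a new start every 30 days. Sample size assumes a rise in testing from 40% to 60%, six clusters, six intervention periods, a two-sided 5% level and 90% power.

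The effect is to be estimated as described under Latent variable analysis and structural equation model: "We will use structural equation model (SEM) to evaluate the effect of HIVST intervention". The same sentence has the model "estimate the association among behavioral intervention theory modules", together with sexual behaviour, testing behaviour, HIV infection and HIVST. The section ends by saying that "multiple model fitting and comparison will be conducted to select the best model that can explain the effect and influencing factors of HIVST intervention". No candidate set and no selection criterion are given.

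The other analysis sections contain no effect estimator:
- Data management and statistical analysis: "the general statistical analysis will be carried out by using standard statistical software and professional statistical software".
- Descriptive statistical analysis: summaries, "including count, frequency, ratio, mean, standard deviation, and so on".
- Missing data: "Multiple imputation (MI) methods will be conducted to increase the robustness of study results".

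Table 2 lists the "HIV testing self-efficacy scale" and the susceptibility, obstacle and benefit perception scales as collected at baseline and at follow-up.

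**The concern.** Randomising the start date supports one clear comparison: testing frequency with the intervention available against testing frequency while waiting, within the same calendar period. The described analysis departs from it in three ways.

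- **Estimand.** If follow-up values of the scales enter the model, they may already have been changed by the intervention. The direct path and the total effect are then different quantities, and the section does not say which one is the answer.
- **Selection.** The model that delivers the effect is chosen on the same data that are then used to test it. A nominal p-value or interval from the retained model does not allow for that choice.
- **Time.** In a stepped wedge, exposed person-time falls later than control person-time. Without period terms, any background trend in testing is credited to the intervention. The article's own Background describes growing promotion of testing and more men taking it up.

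The primary conclusion is at stake: what the reported number means, and whether its test is held at 5%.

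**Working it through.** The plan states no figure on this point, so there is none to reproduce. The steps below show mechanism. All path values and trends are assumptions, in SD units.

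**1. Does the SEM total equal the randomised total?**
Let A be the intervention (half exposed, variance 0.25), M a follow-up scale, U an unmeasured common cause with variance 1, and Y the outcome. Residual variances are 1.
- M = 0.5A + 0.5U + error; Y = 0.15A + 0.3M + 0.5U + error.
- True total effect = 0.15 + 0.5 × 0.3 = 0.30.
- Slope of Y on M given A = 0.3 + 0.5 × 0.5/(0.25 + 1) = 0.50.
- Direct coefficient of A given M = 0.30 − 0.5 × 0.50 = 0.05.
- Saturated SEM, direct plus indirect = 0.05 + 0.5 × 0.50 = 0.30, which is correct.
- SEM with the direct path dropped: Var(M) = 0.0625 + 0.25 + 1 = 1.3125. Cov(M,Y) = 0.15 × 0.5 × 0.25 + 0.3 × 1.3125 + 0.5 × 0.5 = 0.6625. The slope is 0.6625/1.3125 = 0.505, so the SEM total is 0.5 × 0.505 = 0.25.

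A simulation with 408 participants and 500 replicates agreed: unadjusted total 0.298, saturated SEM total 0.298, direct coefficient 0.046, SEM total without the direct path 0.254. The answer therefore depends on which model is kept and which coefficient is read from it.

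**2. Is the 5% level held?**
Keep A→M = 0.5 and U as above, but set the direct path and M→Y to zero, so the true total effect is 0. The coefficient of A given M is 0 − 0.5 × (0.5 × 0.5/1.25) = −0.10. A test of that coefficient is not a 5% test of no total effect. Choosing the model on the same data is a further, separate source of error. Its size depends on the candidate set and the criterion, and the article gives neither.

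**3. What does leaving out period do?**
Take six start groups, one all-control period and then one group switching at each of six steps (assumed layout, periods t = 0 to 6). In period t, t groups are exposed and 6 − t are not.
- Mean exposed period = Σt²/Σt = 91/21 = 4.33.
- Mean control period = Σt(6 − t)/21 = 35/21 = 1.67.
- Gap = 2.67 periods.

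| Trend per period | Added bias | Estimate without period terms (true 0.30) |
|---|---|---|
| 0.02 | 0.053 | 0.35 |
| 0.05 | 0.133 | 0.43 |
| 0.10 | 0.267 | 0.57 |

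Simulation gave 0.355, 0.435 and 0.566 without period terms, and 0.30 to 0.31 with them. A purely within-person before-after contrast does not avoid this. For a start at period s, the means are (s − 1)/2 and (s + 6)/2, a gap of 3.5 periods for every s.

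**The case against.** Four points can be made for the plan.

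1. **A reader might infer that the SEM must yield a mediator-adjusted effect.** The documents do not support that. The section never says the direct path will be reported, nor that follow-up scale values enter as mediators. Table 2 shows only that the values exist. A saturated linear SEM recovers the total effect exactly, as step 1 shows. This objection stands: the fault is that the total effect is not secured, not that it is certainly lost.
2. **A reader might put a number on the selection error by treating the candidate models as independent tests.** 1 − 0.95^k gives 14% for three and 23% for five. The article describes neither independent tests nor choosing on significance, and models fitted to one data set are correlated. Comparing models on fit is ordinary SEM practice. Those figures do not apply here. Nor does the document support any particular mediated share.
3. **The article is condensed and an unseen SAP may specify a conventional model.** This has weight. The section does not call the SEM primary or exclude other models, and the data management section leaves room for more advanced methods. A missing period term alone could be left to an SAP. But the article does not stay silent: it names a method for the effect and a way of choosing the model, and an SAP that follows it inherits both.
4. **Table 3 defines testing before and after the intervention, plus control and intervention time, so a simple contrast is possible.** It is, but no such contrast is stated. A simple before-after one would carry the time confounding of step 3.

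**Conclusion.** The point holds in this form: the only inferential method the article states for the intervention effect leaves direct versus total effect open, picks its model on the trial data without a stated criterion, and gives no period term for a design that randomises the order of start. It therefore does not secure the randomised total effect on testing frequency, nor the two-sided 5% level on which the trial was sized.

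The size of the distortion cannot be derived from the document. The values 0.05, 0.25 and 0.30, and the trend table, rest on assumed paths and trends and show direction only. The conclusion needs no assumption about how much of the effect is mediated. It would lapse if an SAP written before the outcome data were examined already fixes a primary model that does not use the SEM.

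**What to change.** Pre-specify one primary model, for example a count mixed model of HIV testing frequency on randomised intervention status by period. Include period effects and within-participant correlation. Baseline testing frequency and region are optional. Leave out every scale or behaviour measured after crossover. Define exposure by the randomised start. State how reported tests are dated relative to it; the before-and-after definitions in Table 3 need this in any case.

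Keep the SEM and its model comparison as a secondary, exploratory analysis of mechanism. State that no effectiveness claim rests on it, and have it report direct, indirect and total effects separately.

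The cost is wording, a little more analysis work and a less prominent place for the SEM. It needs no added participants or visits.
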